### Investigational Plan

Patients will receive intravenous injections of 7.4 GBq (±10%) of [^177^Lu]Lu-PSMA-617 once every 6 wk (±1 wk) for a maximum of 6 rechallenge cycles. [^177^Lu]Lu-PSMA-617 will be supplied by Novartis in vials for injection. Further details regarding dosage, packaging, labeling, and storage, can be found in sections 4.2.1–4.2.4 of the study protocol.

Patients will undergo hematology, chemistry, and PSA testing twice per cycle. The first time will be either on day 1 or within the 7 days preceding day 1. The second time will be during week 3.

Single-time-point SPECT/CT dosimetry protocol will be performed every cycle. Patients will be imaged with posttreatment quantitative SPECT/CT scans 24 h after administration of [^177^Lu]Lu-PSMA-617 (allowed window, 24–72 h) (15) using an Intevo T6 Dual Detector SPECT scanner with 6-slice CT (Siemens Healthineers). SPECT/CT scans will extend from midthigh to vertex with 3 bed positions. Dosimetry will be performed by using MIM (MIM Software Inc.). More details can be found in section 6.8 of the study protocol. SPECT/CT scans will be used to determine the maximum number of cycles each subject may receive without exceeding the kidney dose threshold (biologically effective dose [BED] of 39 Gy) and to evaluate response to treatment using response assessment criteria.

PSMA PET/CT scans will be performed during week 3 of cycles 2, 4, and 6 using Biograph 64 and mCT scanners (Siemens Healthineers). A single 185-MBq dose (range, 111–2,830 MBq) of [^68^Ga]Ga-PSMA-11 will be administered per PET scan as a bolus intravenous injection. After 50–100 min of uptake, patients will undergo a whole-body (skull to midthighs) PET/CT scan. PET emission scans will be corrected for decay, dead time, random events, and scatter. PET images will be corrected for attenuation using segmented attenuation data of the low-dose CT scan. More details are provided in section 6.7 of the study protocol.

Table 3 details how treatment-related adverse events will be graded and the appropriate management recommendations for each adverse event.

**TABLE 3. tbl3:** Management of Treatment-Related Adverse Events

Adverse event and severity	Management recommendation
Myelosuppression (anemia, thrombocytopenia, leukopenia, or neutropenia)	
Grade 2	[^177^Lu]Lu-PSMA-617 can be given as clinically indicated.
Grade ≥3	Withhold [^177^Lu]Lu-PSMA-617 until improvement to grade 1 or return to baseline, then reduce dose by 20% to 5.9 GBq.
Renal toxicity	
Grade 2 with eGFR < 30 mL/min/1.73 m^2^	Withhold [^177^Lu]Lu-PSMA-617 until improvement or return to baseline.
≥40% increase in serum creatinine and >40% decrease in eGFR compared with baseline	Withhold [^177^Lu]Lu-PSMA-617 until improvement or return to baseline, then reduce dose by 20% to 5.9 GBq.
Grade ≥3	Permanently discontinue [^177^Lu]Lu-PSMA-617.
Dry mouth	
Grade 2	Withhold [^177^Lu]Lu-PSMA-617 until improvement or return to baseline; consider reducing dose by 20% to 5.9 GBq.
Grade 3	Withhold [^177^Lu]Lu-PSMA-617 until improvement or return to baseline, then reduce dose by 20% to 5.9 GBq.
Gastrointestinal toxicity	
Grade ≥3 that is not amenable to medical intervention	Withhold [^177^Lu]Lu-PSMA-617 until resolved to grade 2 or return to baseline, then reduce dose by 20% to 5.9 GBq.
Fatigue	
Grade ≥3	Withhold [^177^Lu]Lu-PSMA-617 until resolved to grade 2 or return to baseline.
Electrolyte or metabolic abnormalities	
Grade ≥2	Withhold [^177^Lu]Lu-PSMA-617 until improvement to grade 1 or return to baseline.
AST or ALT elevation >5 times ULN in absence of liver metastases	Permanently discontinue [^177^Lu]Lu-PSMA-617.
Other nonhematologic toxicity	
Any unacceptable toxicity	Permanently discontinue [^177^Lu]Lu-PSMA-617.
Any serious adverse event that requires treatment delay >4 wk	Permanently discontinue [^177^Lu]Lu-PSMA-617.
Any persistent and intolerable grade ≥2 adverse event	Permanently discontinue [^177^Lu]Lu-PSMA-617.

eGFR = estimated glomerular filtration rate; AST = aspartate transaminase; ALT = alanine transaminase; ULN = upper limit of normal.

During this trial, the only concomitant medications that patients are allowed to continue are androgen-deprivation therapy (e.g., leuprolide, relugolix), first-generation ARPIs (e.g., bicalutamide), local external beam radiotherapy, and concomitant prostate cancer therapies that were administered during the first regimen of [^177^Lu]Lu-PSMA-617 and continued afterward. Any other treatments for prostate cancer must be discontinued before the start of the trial. Second-generation ARPIs (e.g., abiraterone, enzalutamide, darolutamide, apalutamide) do not require a washout period. Chemotherapy agents (e.g., docetaxel, cabazitaxel) require a 6-wk washout period. RPTs (e.g., ^89^Sr, ^153^Sm, ^223^Ra) require a 6-wk washout period. Sipuleucel-T, olaparib, rucaparib, and pembrolizumab require a 4-wk washout period.

### Study Duration

Patients will be treated with up to 6 cycles of [^177^Lu]Lu-PSMA-617 rechallenge therapy. Treatment will be discontinued if there is evidence of biochemical (PSA increase of >25% and 2 ng/mL above nadir) and radiographic (progressive disease on PSMA PET/CT or SPECT/CT) progression, withdrawal of consent, noncompliance, unacceptable toxicity, or evidence that the patient is no longer benefiting or at the discretion of the investigator or sponsor.

The duration of subject participation will be from the time informed consent is provided through the 24 mo following completion of the final cycle of rechallenge therapy. The planned study duration is 45 mo. Study enrollment began August 2024, with an anticipated trial completion date of May 2028. The full schedule of visits and assessments is provided in Figure 3.

**FIGURE 3. fig3:**
[figure not shown]
Schedule of assessments. BPI-SF = Brief Pain Inventory–Short Form; ECOG = Eastern Cooperative Oncology Group; FACT-RNT = Functional Assessment of Cancer Therapy–Radionuclide Therapy.

### Sample Size Determination and Stopping Rule

The primary endpoint of the study is the 12-mo OS rate starting from cycle 1 day 1 of rechallenge therapy. We hypothesize that patients retreated with [^177^Lu]Lu-PSMA-617 will have a 12-mo OS rate of 71% compared with a null hypothesis of 50% with no rechallenge therapy, based on the standard care group of the phase 3 VISION trial (1). A 2-sided, 1-sample log-rank test was used to estimate power. Assuming survival times follow an exponential distribution, a total of 40 subjects will achieve 80% power to detect a difference between a rechallenge group (71%) and a historic control group (50%), using a significance level of 0.05 (2-sided) and a follow-up duration of 24 mo after the last subject is enrolled. The complete statistical analysis plan is provided in section 11 of the study protocol.

The study incorporates a stopping rule mandating termination of the trial if treatment-related serious adverse events occur in 5 of the first 20 patients. If 4 or fewer such events occur among the first 20 patients, the trial can continue to completion. This rule was informed by an expected event rate of approximately 8% rate, as reported in prior retrospective series (6–10), using a 1-sample binomial test (1-sided α = 0.05).

## DISCUSSION

This represents one of the first prospective phase 2 trials of rechallenge therapy for patients with mCRPC whose disease recurs after a favorable response to an initial regimen of [^177^Lu]Lu-PSMA-617 and who may respond favorably if rechallenged. This trial aims to establish both the efficacy of rechallenge therapy, using 12-mo OS as the primary endpoint, as well as the safety of such therapy, using the rate of adverse events as well as multiple quality-of-life measures as secondary endpoints.

The inclusion criteria specify that patients must have had a PSA response, defined as a decrease of at least 50%, during the initial regimen. Patients must also have completed at least 4 cycles of [^177^Lu]Lu-PSMA-617 during the initial regimen, as completing a shorter course likely signaled that the treatment was stopped because of significant adverse effects or disease progression. These 2 inclusion criteria are supported by several retrospective studies that showed favorable outcomes for rechallenge therapy (7–9).

The 12-mo OS rate was chosen to be the primary endpoint because the VISION trial showed such a dramatic OS benefit for [^177^Lu]Lu-PSMA-617 RPT (hazard ratio, 0.62) (1). We hypothesize that the OS benefit of rechallenge therapy will be similar to that observed in the original VISION trial (i.e., approximately 40% mortality reduction). Even though patients may not have as strong of a response to the second regimen of [^177^Lu]Lu-PSMA-617 as they did to the initial regimen, this may be balanced by the fact that this trial is only enrolling patients who responded well to the initial regimen. Using the 12-mo OS rate of 50% from the VISION trial standard-of-care group as a historical benchmark and assuming a mortality reduction of 40% with rechallenge therapy, we hypothesize that we will observe a 12-mo OS rate of greater than 70%. This is the value that was used for the power analysis of the primary endpoint. We decided against using a retrospective cohort of rechallenge therapy as our comparison cohort because of the limitations in sample size, selection bias, and the retrospective nature of data collection.

Prior retrospective data have not established the ideal number of cycles for rechallenge therapy. Reports range from 2 additional cycles to as many as 3 separate courses of 1–6 cycles per course (6–10). We hope to determine how a repeat course of up to 6 additional cycles performs in this patient population.

At the request of the FDA, our study protocol includes dosimetric analyses using a single-time-point SPECT/CT scan after each infusion of [^177^Lu]Lu-PSMA-617. The FDA raised the issue that, between the 2 regimens of [^177^Lu]Lu-PSMA-617 as well as any prior external beam radiotherapy, patients may exceed the maximum dose constraint for the kidneys. This constraint has been established as a BED of 39 Gy, using data from peptide receptor RPT (16). The protocol was modified to specify that if the calculated kidney BED exceeds 39 Gy, the total number of cycles must be adapted or limited to remain under the 39-Gy BED limit.

When the trial began, there was an additional inclusion criterion that patients must have had at least 1 course of prior chemotherapy, consistent with FDA indications for [^177^Lu]Lu-PSMA-617 RPT. This was removed in a protocol amendment after results from the PSMAfore trial showed that chemotherapy-naïve patients had a radiographic PFS benefit with [^177^Lu]Lu-PSMA-617 compared with a change in ARPI therapy (17), which led to FDA approval of [^177^Lu]Lu-PSMA-617 in chemotherapy-naïve patients as well.

Since this study began, we have considered several exploratory analyses. The first includes studying how the presence of concomitant medications affects OS and PSA response. This question has not been addressed by existing retrospective data. We plan to compare patients receiving any concomitant medication with patients receiving no concomitant medications using log-rank analysis. We also plan to compare patients receiving androgen-deprivation therapy or first-generation ARPIs with those who continued second-generation ARPIs using log-rank analyses. The second exploratory analysis includes evaluating whether the length of time between the initial [^177^Lu]Lu-PSMA-617 course and subsequent PSA progression affects OS and PSA response rates. We plan to compare patients with time intervals less than 12 mo versus time intervals greater than or equal to 12 mo using log-rank analysis.

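### The 71% target for 12-month survival is not the VISION-sized effect it is said to be: on the hazard scale that effect gives 65–66%, and 71% needs a hazard ratio of about 0.49

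*Protocol article*

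**What the plan says.** The Discussion of the protocol article builds the target in four steps.

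- It gives the VISION result on the hazard scale: "the VISION trial showed such a dramatic OS benefit for [^177^Lu]Lu-PSMA-617 RPT (hazard ratio, 0.62".
- It expects a rechallenge benefit "similar to that observed in the original VISION trial (i.e., approximately 40% mortality reduction".
- It starts from 50%, "Using the 12-mo OS rate of 50% from the VISION trial standard-of-care group as a historical benchmark", and then, "assuming a mortality reduction of 40% with rechallenge therapy, we hypothesize that we will observe a 12-mo OS rate of greater than 70" per cent.
- It ties this to the design: "This is the value that was used for the power analysis of the primary endpoint".

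The section on sample size and stopping fixes the alternative: retreated patients "will have a 12-mo OS rate of 71% compared with a null hypothesis of 50% with no rechallenge therapy". The model behind the power figure is given there as well: "Assuming survival times follow an exponential distribution", a two-sided one-sample log-rank test at 0.05, 40 patients, 80% power, and 24 months of follow-up after the last enrolment. The Endpoints section names the same log-rank test for the analysis and uses Kaplan–Meier for estimation with a confidence interval.

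**The concern.** A hazard ratio multiplies the cumulative hazard. It does not multiply the probability of being dead at 12 months. When half the patients are expected to die by that time, the two scales give clearly different answers. The article takes a hazard ratio, renames it a mortality reduction of about 40%, and reaches a figure that follows only on the risk scale.

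Two statements then conflict. One is that the assumed benefit resembles VISION's. The other is that 12-month survival will be 71%. A reader is told that the trial has 80% power for a VISION-sized benefit, when the power statement concerns a larger one. If the true benefit did match VISION's, survival of about 65% would fall short of the hypothesised 71% and could be misread as a weak result for rechallenge.

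**Working it through.** **Inputs.** From the article: null 12-month survival 50%; alternative 71%; VISION hazard ratio 0.62, restated as about a 40% reduction; exponential survival; one-sample log-rank test, two-sided 0.05; 40 patients; 24 months of follow-up after last enrolment. Accrual length is not stated. I assume 0 to 21 months, where 21 is the 45-month study duration minus 24.

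**Step 1: how the article gets to about 70%.** On the risk scale, survival = 1 − 0.50 × (1 − 0.40) = 70.0%. With 0.62 in place of 0.60 it is 1 − 0.50 × 0.62 = 69.0%. Risk arithmetic therefore lands next to the article's figure, though it does not quite reach 71%.

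**Step 2: the same effect on the hazard scale.** Under proportional hazards, of which the exponential model is a case, S1 = S0^HR.

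- HR 0.62: 0.5^0.62 = 65.1%
- HR 0.60: 0.5^0.60 = 66.0%

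**Step 3: the hazard ratio that the target implies.** HR = ln(S1)/ln(S0).

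- 71%: ln(0.71)/ln(0.5) = 0.494, about a 51% hazard reduction
- 70%: ln(0.70)/ln(0.5) = 0.515

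**Step 4: power at n = 40.** The null hazard is ln(2)/12 = 0.0578 per month. For each patient the expected deaths under the null are 0.0578 times the observed time. Let O be the observed and E the total expected deaths. The statistic is (O − E)/√V, with V = E or V = (O + E)/2 as two common variance forms. Simulated power over both forms and over accrual of 0–21 months:

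| True effect | Stated follow-up (24 months after last enrolment) | Test restricted to first 12 months (not stated) |
|---|---|---|
| 71% (HR 0.494) | 92–97% | 74–81% |
| 66.0% (HR 0.60) | 71–83% | – |
| 65.1% (HR 0.62) | 66–78% | 44–53% |

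Closed-form approximations for the stated follow-up are a little lower: 89–95% at 71%, 69–78% at HR 0.60 and 64–73% at HR 0.62. By those formulas 40 patients reach 80% power at a hazard ratio of about 0.55–0.59, a 12-month survival of roughly 66–68%.

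**The plan's own figure.** The stated 80% at 71% does not reproduce from the stated inputs, which give more. Values near 80% appear under other set-ups, for example a log-rank test limited to 12 months of data, but the article does not describe one.

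**The case against.** **The wording may mean a reduction in risk.** A mortality reduction can be read as fewer deaths by 12 months, and then 70% is correct arithmetic. But the article equates that reduction with the VISION effect, and the only VISION effect that it gives is a hazard ratio. Its remark about enrolling prior responders is offered to balance a weaker second response, not to justify a larger effect.

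**The mechanism is inferred.** This stands. Risk arithmetic gives 70.0% or 69.0%, not 71%, so confusing the two scales is the likely origin but does not fully explain the figure. Section 11 of the full protocol, which holds the analysis plan, is not shown. The mismatch between 71% and a VISION-sized effect does not depend on how it arose.

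**The design has slack.** This also stands, and it limits the consequence. With the stated test and follow-up, 40 patients have well over 80% power at 71% and come near 80% at hazard ratio 0.60 if accrual is long.

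**A stronger reading to avoid.** A reader might infer that the trial has adequate power only at a hazard ratio of 0.49 and only about 45% power for a VISION-sized benefit. The documents do not support that. Figures that low need an exact or Kaplan–Meier test at month 12, which is not the named test, or a log-rank test cut off at 12 months, which is not stated. The 12-month wording of the endpoint leaves the cut-off possible, so those figures are conditional.

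**Conclusion.** The derivation is wrong as written. On the scale of the article's own model, the effect it cites corresponds to 65.1–66.0% at 12 months, and 71% assumes a hazard ratio of about 0.49. The gap is 5 to 6 percentage points of 12-month survival.

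Under the stated test, the chance of missing a VISION-sized benefit (hazard ratio 0.62) is about 22–34%, against the 20% that 80% power implies. At hazard ratio 0.60 it is about 17–29%. That is a moderate shortfall, small or absent at the favourable end, and it does not show that the trial is too small. The 80% quoted for 71% is also unsupported by the stated inputs, which give about 92–97%.

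These power figures rest on exponential survival, uniform accrual over an assumed 0–21 months, no loss to follow-up, and use of all follow-up in the test. The conversion in steps 2 and 3 needs only proportional hazards.

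**What to change.** 1. In the Discussion, correct the derivation. Either give 65–66% as the VISION-equivalent 12-month survival, or keep 71%, state that it assumes a hazard ratio of about 0.49, and drop the claim that this matches VISION.
2. In the sample-size section, rerun the power calculation with the accrual period stated, and say whether the log-rank test uses all follow-up or only the first 12 months.
3. Report power at 40 patients for both 65–66% and 71%, in place of the single 80%. Relabelling 71% as a hazard ratio of 0.49 while leaving 80% beside it would keep an unsupported figure.

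The cost is text and one recalculation. The reported power for the expected effect may become slightly less favourable. No patients are added.

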## CONCLUSION

The RE-LuPSMA trial is a prospective phase 2 trial studying the efficacy and safety of [^177^Lu]Lu-PSMA-617 rechallenge therapy. This has the potential to establish an alternative therapeutic option for patients with progressive mCRPC after a favorable response to an initial regimen of [^177^Lu]Lu-PSMA-617.
